## **2.2 Rationale**

This study is designed to provide an evidence base to inform future NHS investment in health care services for children and young people with T1DM. The role of intensive insulin therapy in optimizing glycaemic control and thereby reducing the risk of vascular complications of T1DM is unquestioned however the optimal way in which to achieve this and the cost effectiveness of the tools currently available is unknown. This study will compare two methods of insulin delivery during childhood and adolescence to identify which facilitates superior glycaemic control, and examine the impact of treatment modalities on other predictors of vascular complications of T1DM, adverse events and QoL.

The recruitment of children to a randomised controlled trial of two insulin delivery systems is likely to be unsuccessful in children and young people with established diabetes in whom preference is likely to exclude them from randomisation or strongly influence the successful use of the therapy. For this reason this study will recruit patients at the time of diagnosis.

However, we are aware of the potential difficulties recruitment at the time of diagnosis poses. For this reason we propose an inbuilt pilot study to test the feasibility of recruiting a cohort of patients who are representative of the background population of children and young people with diabetes.

## 2.3 Objectives

### Inbuilt pilot study

#### **Primary Objective:**

To acquire an understanding of the acceptability of randomisation to MDI or CSII at diagnosis of T1DM in children and young people.

#### **Secondary Objectives:**

To define the characteristics of patients who consent and those who do not consent to randomisation.

To use the data as an internal pilot to check the size of the standard deviation used in the sample size calculation of the full study.

### Full study

#### **Primary Objective:**

To compare the glycaemic control assessed by HbA1c at 12 months after diagnosis in children and adolescents receiving CSII with those receiving MDI.

#### **Secondary Objectives:**

To compare the following:

Clinical effectiveness of children and adolescents receiving CSII with those receiving MDI.

The safety of children and adolescents receiving CSII with those receiving MDI.

Growth of children and adolescents receiving CSII with those receiving MDI

The quality of life of children and adolescents receiving CSII with those receiving MDI

Cost effectiveness of providing insulin to children and adolescents by CSII compared to MDI.

## **2.4 Potential Risks and Benefits**

### **2.4.1 Potential Risks**

When potentially eligible children and young people are identified, their parent or person with parental responsibility will be approached by the investigator, or a designated member of the investigating team, during which an opportunity will be given to understand the objectives, risks and inconveniences of the trial. Although insulin glargine is unlicensed for use in children aged less than 2 years, the insulin analogues and devices under investigation are those routinely used in children with T1DM. We do not anticipate any increase in adverse events associated with the use of either delivery method over and above the complications normally seen in routine clinical care.

### **2.4.2 Known Potential Benefits**

The NICE guideline recognises that intensive therapy (MDI or CSII) offers greater potential to optimise glycaemic control and minimise long term complications than conventional insulin regimes of twice daily pre-mixed insulin. For this reason, NICE recommends that all children and young people should be offered intensive therapy from the time of diagnosis in the form of MDI. Children aged 12 and above should have access to CSII where HbA1c levels below 8.5% cannot be achieved without disabling hypoglycaemia despite high levels of care and children under 12 years should have access to CSII from diagnosis where MDI is considered impractical or inappropriate. Participants recruited to this study will be randomly allocated one of these two intensive therapies (CSII or MDI). Children recruited to the study aged 12 years or more will have access to CSII at diagnosis, a treatment currently not recommended at diagnosis by NICE. However, in participants aged less than 12 years of age participation will eliminate patient and family choice of insulin delivery system.

There are currently no data from which patients, parents or health care professionals can draw to inform their selection of insulin delivery device. Although the element of choice will be removed from participants recruited to this study, we believe this is acceptable given that there is no evidence demonstrating the superiority of either treatment. All data generated by this study will be closely monitored by the Independent Data and Safety Monitoring Committee (IDSMC). All patients and clinical teams will be advised of the findings and a decision will be made locally whether or not to offer the superior treatment on the basis of the individual's glycaemic control.

### **3 SELECTION OF CENTRES/CLINICIANS**

Centres meeting the following criteria will be selected for the study. The SCIPi trial will take place in paediatric diabetes outpatient clinics/ ward or A&E unit (centres) in the UK. The study will be coordinated through the Medicines for Children Clinical Trial Unit (MC-CTU), the Diabetes Research Network (DRN) and the Comprehensive Clinical Research Network (CCRN). Study centres will be initiated once all local R&D approval and study-specific conditions (e.g. training requirements) have been met, and all necessary documents have been returned to MC-CTU. Initiation meetings will cover the requirements outlined in CTRC SOPs TM017 and TM018.

#### **3.1 Centre/Clinician Inclusion Criteria**

Any paediatric diabetes outpatient clinic/ ward or A&E unit based within NHS can participate in the trial provided the following criteria's are met:

- a. Experience in managing 10 or more patients treated with CSII and currently offer MDI regimen;
- b. Multidisciplinary team including paediatric consultant, dietician, diabetes nurse and other medical staff all trained in the care of children with diabetes;
- c. Local R&D approval;
- d. Signed non-commercial agreement between the centre and the sponsor;
- e. Completion of the 'Signature and Delegation Log';
- f. Receipt of evidence of completion of (c), (d) and (e) by the MC-CTU.

#### **3.2 Centre/Clinician Exclusion Criteria**

- a. Not meeting the inclusion criteria listed above

## 4 TRIAL DESIGN

This is an open labelled 2-arm multi-centre randomised controlled trial comparing continuous subcutaneous insulin infusion (CSII) with multiple daily injections (MDI) of insulin in 316 children and young people aged 7 months to 15 years who have been newly diagnosed with type 1 diabetes mellitus. Patients should be approached and consented as soon after diagnosis as possible. Participants will be randomised in a 1:1 ratio to either of the two treatments (MDI or CSII pumps). Training will be given to all the participants and their parents regarding use of the intervention(s) and randomised treatment will be started within 14 days of diagnosis. The study includes an internal pilot with a sample size of 30 participants to estimate the rate of consent to randomisation and to define the characteristics of recruited participants.

### 4.1 Pilot Study

An inbuilt pilot study (n=30) will test the feasibility of recruitment to this study protocol. The full study (n=316) will open if the following criteria are met:

- a. Fifty percent or more patients who are eligible and are invited to participate in the pilot study are successfully recruited;
- b. Demographic characteristics like age, ethnicity, gender and deprivation score are not considered to be significantly different in the group of patients who are recruited compared to those who decline. These characteristics are significantly associated with glycaemic control (24-26)

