### **9.4 Sample Size**

#### **Internal pilot**

Thirty subjects will be recruited. 30 patients provides 80% power to detect a drop in the consent rate to 25% from the assumed 50%, at the 5% significance level.

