### **9.5 Interim Monitoring and Analyses**

Interim analyses of the accumulating data will be performed at regular intervals (at least annually) for review by the IDSMC. The IDSMC members will comply with a trial-specific IDSMC charter according to International Conference on Harmonisation Good Clinical Practice (ICH GCP) guidelines. These analyses will be performed at the MC-CTU by the trial statistician in accordance with the Standard Operating Procedures of the CTRC. The trial statistician at the MC-CTU will prepare the report for the IDSMC, the contents of which will be agreed by the IDSMC.

The data collected during the pilot phase will be used to check the estimate of the common standard deviation used in the sample size calculation of the full trial. The estimate obtained may be used to increase but not decrease the trial sample size. No formal comparisons of the trial primary outcome are planned at any interim analyses. If requested by the IDSMC the comparison will be made and the Peto-Haybittle stopping rule used to inform discussions.

The IDSMC will be asked to give advice on whether the accumulated data from the trial, together with results from other relevant trials, justifies continuing recruitment of further patients or further follow-up.

The full trial will open if the criteria listed in section 4.1 are met. A decision to discontinue recruitment, in all participants or in selected subgroups will be made only if the result is likely to convince a broad range of clinicians including participants in the trial and the general clinical community. If a decision is made to continue, the IDSMC will advise on the frequency of future reviews of the data on the basis of accrual and event rates. The IDSMC will make recommendations to the TSC (TSC, see section 16) as to the continuation of the trial.

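### The 80% power and 5% level stated for the 30-patient pilot belong to a different rule and denominator from the 50% consent criterion that opens the full trial

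*Protocol*

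**What the plan says.** Three places in the protocol bear on the pilot decision.

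- **Section 4.1 (Pilot Study)** sets the gate: "The full study (n=316) will open if the following criteria are met". Criterion (a) is "Fifty percent or more patients who are eligible and are invited to participate in the pilot study are successfully recruited". Criterion (b) asks that demographic characteristics "are not considered to be significantly different in the group of patients who are recruited compared to those who decline".
- **Section 9.4 (Internal pilot)** gives the size and its justification: "Thirty subjects will be recruited", and "30 patients provides 80% power to detect a drop in the consent rate to 25% from the assumed 50" per cent, "at the 5% significance level". It does not say whether the test is one- or two-sided.
- **Section 9.5 (Interim Monitoring and Analyses)** repeats the gate: "The full trial will open if the criteria listed in section 4.1 are met". It adds no test, confidence limit or lower boundary for consent.

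Section 4 (Trial Design) likewise describes the pilot as 30 participants, whose purpose includes estimating the consent rate.

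**The concern.** The power sentence and the gate describe two different rules for one decision, in two respects.

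1. **Cut-off.** A test with 80% power against 25% gives an adverse result only when observed consent is well below 50%. Criterion (a) gives an adverse result whenever observed consent is below 50% at all. Because the cut-off equals the assumed rate, sampling variation alone makes the outcome close to even when the assumption is exactly right.
2. **Denominator.** A consent rate is recruits divided by patients invited. The power calculation uses 30 as the number invited; the protocol fixes 30 as the number recruited.

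Anyone reading section 9.4 would expect a small chance of an adverse result at 50% consent and an 80% chance at 25%. Neither figure applies to the gate. The committee that acts on the result needs the gate's own error rates.

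**Working it through.** **Inputs.** Pilot size 30, assumed rate p0 = 0.50, alternative p1 = 0.25, level 5% and power 80% (section 9.4); go if recruited / (eligible and invited) is at least 0.50 (section 4.1). Assumption: each invited patient consents independently with the same probability p.

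**Step 1: reproduce the stated 80%.** Take X ~ Binomial(30, p), with 30 as the number approached. An exact two-sided 5% test allows at most 0.025 in the lower tail:

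- P(X ≤ 9 | 30, 0.50) = 0.0214, so the test rejects at 9 or fewer, i.e. 9/30 = 30%.
- Power = P(X ≤ 9 | 30, 0.25) = 0.803.

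This matches the protocol. The two-sided normal and arcsine approximations give 0.816 and 0.818. A one-sided exact test rejects at 10 or fewer, with level 0.049 and power 0.894, so the two-sided reading fits best.

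**Step 2: denominator as written.** With 30 recruited, the expected number invited is about 30/0.50 = 60 at the assumed rate, and 30/0.25 = 120 at the alternative.

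**Step 3: operating characteristics of criterion (a).** If invitations continue until 30 are recruited, criterion (a) is met when no more than 60 were invited. That is the same event as at least 30 consenting among the first 60, so P(met) = P(X ≥ 30 | 60, p). If 30 is instead read as the number invited, P(met) = P(X ≥ 15 | 30, p).

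| True consent | Met, 30 recruited | Met, 30 invited |
|---|---|---|
| 25% | < 0.1% | 0.3% |
| 40% | 7.5% | 17.5% |
| 45% | 25.8% | 35.5% |
| 50% | 55.1% | 57.2% |
| 55% | 81.8% | 76.9% |
| 60% | 95.6% | 90.3% |

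**Step 4: compare the two rules.**

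| Chance of an adverse result | At 50% consent | At 25% consent |
|---|---|---|
| Test behind section 9.4 (9 or fewer of 30) | 2.1% | 80.3% |
| Criterion (a), 30 recruited | 1 − 0.551 = 44.9% | > 99.9% |
| Criterion (a), 30 invited | 1 − 0.572 = 42.8% | 99.7% |

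**Step 5: precision of the observed rate.** With 60 invited and p = 0.50, the standard error is √(0.25/60) = 0.065, so the approximate 95% sampling range is ±1.96 × 0.065, or about ±13 percentage points. An observed rate just under 50% is fully compatible with the assumed rate.

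**The case against.** The case on the other side has four parts.

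- **The 80% is correct as arithmetic, and 50% may be a deliberate feasibility target.** Both points stand. The figure reproduces, and how much consent is enough is for the sponsor to choose. But if 50% is the target, the power sentence neither describes the gate nor justifies 30 recruits for it.
- **Any point-estimate cut-off gives near-even odds at the cut-off itself, and this one is strict against poor consent.** This also stands. At 25% the criterion is missed more than 99% of the time, against the 80% stated, and at 60% it is met 96% of the time. The difficulty is that the cut-off coincides with the planning assumption and that the protocol reports another rule's error rates.
- **Missing the criterion is not the same as stopping.** A reader might infer that the trial is stopped 45% of the time when consent is as planned. The protocol does not fix that. Section 9.5 limits when recruitment would be discontinued, and section 16.2 leaves the ultimate decision on continuation to the steering committee. The 45% is the chance of missing criterion (a).
- **Criterion (b) cannot be quantified from the text.** A reader might infer that it fails by chance about 19% of the time, from 1 − 0.95⁴ = 0.185. That requires four independent 5% tests. Section 4.1 names no test, gives its characteristics as examples, and leaves room for judgement. No figure for (b) is relied on here.

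**Conclusion.** The inconsistency is real and of moderate severity. The 5% and 80% in section 9.4 belong to a test on 30 patients approached that rejects at 30% or less; the criterion in sections 4.1 and 9.5 requires at least 50% observed among those invited to yield 30 recruits. Under that criterion, consent exactly as assumed misses the gate 44.9% of the time (42.8% if 30 are invited), where the test in section 9.4 would give an adverse result 2.1% of the time.

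The result rests on independent consent decisions with a common probability, on recruitment continuing to exactly 30, and on criterion (a) alone. The direction is the same under either reading of the denominator. The near-even odds apply at 50% true consent and should not be extended to a trial with comfortably higher consent.

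The point does not touch the primary comparison, its type I error or the full-trial sample size.

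**What to change.** Align sections 4.1 and 9.4.

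1. State that the denominator is eligible patients invited, and that 30 is the number recruited.
2. If the 50% point-estimate criterion is kept, delete the 80% power sentence and give the criterion's own operating characteristics: met with probability under 0.1%, 26%, 55%, 82% and 96% at true consent of 25%, 45%, 50%, 55% and 60%. Add that an observed rate just under 50% is compatible with the assumed rate, so that the steering committee can weigh it.

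A significance-based lower boundary is an option for the sponsor and not a required correction. For example, an adverse result at 21 or fewer of 60 invited has a 1.4% chance at 50% consent and 97% at 25%. The price is a lower feasibility standard: at true consent of 40% it would let the trial continue about 74% of the time, against 7.5% under the written criterion.

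The cost is wording in two sections. The protocol does not say whether the pilot decision has already been taken; if it has, only the description and the trial report need correcting.

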### 4.2 Full Trial

#### Primary Endpoint

Glycaemic control (HbA1c) 12 months after diagnosis.

#### Secondary Endpoint(s)

- a. Percentage of participants in each group with HbA1c <6.5%
- b. Incidence of severe hypoglycaemia
- c. Incidence of diabetic ketoacidosis
- d. Change in BMI SDS
- e. Height
- f. Insulin requirements (units / kg /day)
- g. PedsQL
- h. Incremental cost per QALY gained
- i. Partial remission

On or near completion of the 12 month study permission will be sought from participants and their carers for ongoing submission of routine clinical data to the research team for a further nine years to enable long term outcomes to be reported. This will include:

- a. HbA1c;
- b. Insulin treatment regimen;
- c. BMI;
- d. Insulin dose (units/kg/day);
- e. Serious adverse events;
- f. Complications of T1DM.

## **5 STUDY POPULATION**

### **5.1 Inclusion Criteria**

Patients with the following characteristics will be eligible for inclusion in the trial:

- a. Newly diagnosed T1DM using standard diagnostic practice (27);
- b. Age 7 months – 15 years (inclusive);
- c. Parent/legal representative of the patient are willing to give consent for the study;
- d. Parent/legal representative of the patient are able to comply with the treatment regimen and study visits.

### **5.2 Exclusion Criteria**

Patients with the following characteristics will be excluded from the trial:

- a. Treated previously for diabetes;
- b. Haemoglobinopathy;
- c. Co-existing pathology conditions likely to affect glycaemic control, e.g. cystic fibrosis;
- d. Psychological or psychiatric disorders, e.g. eating disorder;
- e. Receipt of medication likely to affect glycaemic control, e.g. systemic or high dose topical corticosteroid or growth hormone therapy;
- f. Allergy to a component of insulin aspart or insulin glargine;
- g. Have a sibling with existing T1DM
- h. Known thyroid condition in a non euthyroid state and;
- i. Known Coeliac disease unable to maintain a gluten free diet.

### **5.3 Participant Transfer and Withdrawal**

In consenting to the trial, participants are consenting to trial treatment, follow-up and data collection. If voluntary withdrawal occurs, the participant (or parent/legal representative) should be asked to allow continuation of scheduled evaluations, complete an end-of-study evaluation, and be given appropriate care under medical supervision until the symptoms of any adverse event resolve or the participant's condition becomes stable. Follow-up of these participants will be continued through the research nurse and the lead investigator at each centre and, where these are unsuccessful, through the child's local paediatric diabetic service or via their GP.

The research team plans to work with the DRN and the CCRN to enable ongoing observation of participants as they move from paediatric to adult health care services. This ongoing observation will be the focus of a separate application for funding.

#### **5.3.1 Participant Transfers**

For the participants moving from the area, every effort should be made for the participant to be followed-up at another participating trial centre and for this trial centre to take over responsibility for the participant or for follow-up at the local paediatric diabetic service or via their GP.

A copy of the participant case report forms (CRFs) and other study related documents should be provided to the new centre. The participant (or parent/legal representative) will have to sign a new consent form at the new site, and until this occurs, the participant

remains the responsibility of the original centre. The MC-CTU should be notified in writing of participant transfers.

### **5.3.2 Withdrawal from Trial Intervention**

Participants may be withdrawn from treatment for any of the following reasons:

- a. Parent/ legal representative (or, where applicable, the participant) withdraws consent.
- b. Intercurrent illness preventing further treatment.
- c. Any change in the participant's condition that justifies the discontinuation of treatment in the clinician's opinion.

If a participant wishes to withdraw from trial treatment, centres should nevertheless explain the importance of remaining on trial follow-up, or failing this, of allowing routine follow-up data to be used for trial purposes. Generally, follow-up will continue unless the participant explicitly also withdraws consent for follow-up (see section 5.3.3).

### **5.3.3 Withdrawal from Trial Completely**

Participants are free to withdraw consent at any time without providing a reason. Although a participant or parent/legal representative is not obliged to give his/her reason(s) for withdrawing prematurely from a trial, the investigator should make a reasonable effort to ascertain the reason(s), while fully respecting the participant's rights. Participants who wish to withdraw consent for the trial will have anonymised data collected up to the point of that withdrawal of consent included in the analyses. The participant will not contribute further data to the study and the MCRN should be informed in writing by the responsible physician and a withdrawal CRF should be completed. Data up to the time of withdrawal will be included in the analyses unless the participant explicitly states that this is not their wish.

If the participant explicitly states that they wish to withdraw from the trial completely and that they do not want their data to be included in the final analyses, please contact the SCIP trial coordinator to request a Participant Data Withdrawal CRF.

## 6 ENROLMENT AND RANDOMISATION

### 6.1 Screening

All patients who are newly diagnosed with T1DM aged 7 months -15 years (inclusive) at the study centres will be screened to identify potentially eligible participants for the study.

Potentially eligible participants (i.e. those that meet the eligibility criteria listed in section 5) and their parent or legally acceptable representative will be invited to participate in the study and provided with the patient information sheet and consent form. The family will be allowed sufficient time to discuss the trial and decide whether to consent to trial entry (see section 11.3 for consent procedures). Providing information, discussing the study and obtaining informed consent should occur as close to the time of diagnosis as possible, ideally between the time of diagnosis (Day 0) and Day 5. Once consented, baseline data should be collected, the participant should be randomised (see section 6.2 and 6.3) and the randomised treatment should be started within 14 days of diagnosis (see section 7).

A 'Screening log' will be maintained of all the patients who undergo screening regardless of whether they decide to participate in the study. Reasons for not being eligible and timelines for providing information and approaching the patient for consent will be recorded. Reasons for declining to participate will be asked routinely but it will be made clear that patients, parents or carers do not have to provide a reason unless happy to do so.

